## Abstract

**Background:**

The introduction of programmed cell death protein 1 (PD-1) blockers (i.e. nivolumab and pembrolizumab) has significantly improved the prognosis of patients with advanced melanoma. However, the long treatment duration (i.e. two years or longer) has a high impact on patients and healthcare systems in terms of (severe) toxicity, health-related quality of life (HRQoL), resource use, and healthcare costs. While durable tumour responses have been observed and PD-1 blockade is discontinued on an individual basis, no consensus has been reached on the optimal treatment duration. The objective of the Safe Stop trial is to evaluate whether early discontinuation of first-line PD-1 blockade is safe in patients with advanced and metastatic melanoma who achieve a radiological response.

**Methods:**

The Safe Stop trial is a nationwide, multicentre, prospective, single-arm, interventional study in the Netherlands. A total of 200 patients with advanced and metastatic cutaneous melanoma and a confirmed complete response (CR) or partial response (PR) according to response evaluation criteria in solid tumours (RECIST) v1.1 will be included to early discontinue first-line monotherapy with nivolumab or pembrolizumab. The primary objective is the rate of ongoing responses at 24 months after discontinuation of PD-1 blockade. Secondary objectives include best overall and duration of response, need and outcome of rechallenge with PD-1 blockade, and changes in (serious) adverse events and HRQoL. The impact of treatment discontinuation on healthcare resource use, productivity losses, and hours of informal care will also be assessed. Results will be compared to those from patients with CR or PR who completed 24 months of treatment with PD-1 blockade and had an ongoing response at treatment discontinuation. It is hypothesised that it is safe to early stop first-line nivolumab or pembrolizumab at confirmed tumour response while improving HRQoL and reducing costs.

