## Study endpoints and analyses

### Primary endpoint

The primary endpoint of this study is the rate of ongoing response according to RECIST v1.1 [34] at 24 months (from first start of treatment with PD-1 blockade).

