#### Analysis of the primary endpoint

The rate of ongoing response at 24 months (or equivalently progression-free survival [PFS] from start of treatment) will be estimated using the Kaplan-Meier method and its one-sided 95% confidence interval (CI) (as the lower boundary of a two-sided 90% CI). These results will be compared with the response rate of a well-defined historical cohort of first-line treatment with pembrolizumab in advanced melanoma (KEYNOTE-006) [5]. Among all patients who had a CR or PR in the KEYNOTE-006, 39% of patients completed 24 months of treatment and had an ongoing response at treatment discontinuation. A 29% ongoing response rate at 24 months after treatment start in patients who early discontinue treatment is considered acceptable, as the current protocol will include less selected patients from clinical practice and patients will have the option to restart treatment with nivolumab or pembrolizumab at PD, thereby potentially achieving a second tumour response. The study will be declared positive for the primary endpoint if the one-sided 95% CI is higher than 29%. The two-sided 90% CI will be constructed using the generalised Brookmeyer and Crowley method based on a g-transformed CI [40, 41].

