### Secondary endpoints

The secondary endpoints include best overall response, duration of response after discontinuation of PD-1 blockade, the need and outcome of rechallenge with PD-1 blockade, and changes in SAE(s). After discontinuation of PD-1 blockade, changes in HRQoL (FACT-M, EuroQol EQ-5D, CWS) will be measured at different time points and compared with patients without early discontinuation of PD-1 blockade. In addition, measurements will be performed to determine the impact of treatment discontinuation on healthcare resource use, productivity losses (RUQ-M by iMTA), and hours of informal care.

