#### Control group

For statistical analyses, the results will be compared with a well-defined historical cohort of first-line treatment with pembrolizumab in advanced melanoma (KEYNOTE-006) [5]. In addition, data will be obtained from the DMTR, which prospectively registers clinical data and HRQoL of all patients with advanced and metastatic melanoma who are treated in the Netherlands [42].

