### Sample size calculation

The sample size was estimated using the principles of an A-Hern design powered for 39% of ongoing response at 24 months. In order to be able to reject 29% under the alternative of 39% with a one-sided type I error of 5 and 90% power, 190 patients will be needed. Criterion for success according to the A’Hern design would be that at least 66 patients out of 190 patients continue to experience a response at 24 months after the first start of treatment. However, the primary test will be done using the lower boundary of the one-sided 95% CI of the Kaplan-Meier estimate of PFS from the start of treatment (which in this patient population is equivalent to an ongoing response) at 24 months to be able to account for possible drop-out or censoring before this time point. Taking a safety margin of 5% for lost to follow-up, the total sample size will be fixed at 200 patients.

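### The abstract's comparison group is chosen by what happened later (24 months completed, still responding), which biases the secondary comparisons and disagrees with the body of the protocol

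*Protocol article*

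**What the plan says.** The protocol article describes its comparison group in four places, and the descriptions differ.

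- **Abstract, Methods.** After listing response, rechallenge, adverse events, quality of life, resource use, productivity and informal care, it says the results will be compared with "patients with CR or PR who completed 24 months of treatment with PD-1 blockade and had an ongoing response at treatment discontinuation".
- **Analysis of the primary endpoint.** The benchmark has a wider denominator: "Among all patients who had a CR or PR in the KEYNOTE-006, 39% of patients completed 24 months of treatment" and were still responding when they stopped.
- **Secondary endpoints.** Changes in quality of life will be "compared with patients without early discontinuation of PD-1 blockade". No comparator is named there for serious adverse events, resource use or productivity.
- **Control group.** KEYNOTE-006 is named as the historical cohort, followed by: "In addition, data will be obtained from the DMTR, which prospectively registers clinical data and HRQoL" of all Dutch patients with advanced disease. Neither source is restricted to completers or to ongoing responders.

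Trial patients enter differently. Under Study population they qualify at confirmed complete or partial response while on treatment, and plan to stop within 6 (+1) weeks of confirmation. Under Follow-up, their data are collected until the end of the study, death, withdrawal or another reason for leaving.

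**The concern.** In the abstract's wording, whether someone counts as a comparator is settled by events after the point at which a Safe Stop patient would have enrolled. A responder who progresses, dies or stops for toxicity between confirmation and 24 months drops out of the comparator. A Safe Stop patient with a later progression, late toxicity or retreatment stays in. The quality-of-life comparator under Secondary endpoints has a milder form of the same problem, because not having stopped early is also known only afterwards.

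The trial has one arm, so every comparative statement on adverse events, quality of life and costs rests on this external group. The abstract hypothesises that early stopping is safe, improves quality of life and reduces costs, and says a favourable result may change standard care. A comparator selected on good outcomes can hide a real gain in quality of life and can overstate a saving.

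**Working it through.** **1. The plan's own figures, to see whether this point touches them.** Inputs from Sample size calculation: 29% against 39%, "with a one-sided type I error of 5 and 90% power, 190 patients will be needed", success at 66 or more responders.

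- Type I error: P(X ≥ 66 | n = 190, p = 0.29) = 0.04995.
- Power: P(X ≥ 66 | n = 190, p = 0.39) = 0.9003.
- 190 is the smallest n meeting both limits in an exact search over 150 to 229.
- Loss to follow-up: 190 / 0.95 = 200.

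All stated figures reproduce. The decision rule is also independent of the comparator: "The study will be declared positive for the primary endpoint if the one-sided 95% CI is higher than 29" percent. That threshold is fixed and was set against 39% of all KEYNOTE-006 responders, with non-completers in the denominator.

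**2. The definitions side by side.**

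| Place | Group | Known at trial entry? |
|---|---|---|
| Abstract | Responders who completed 24 months and still respond | No |
| Analysis of the primary endpoint | All responders (39% meet the abstract's definition) | Response yes; the 39% is an outcome |
| Secondary endpoints (quality of life) | Patients who did not stop early | No |
| Control group | KEYNOTE-006 and DMTR, no completer restriction | No rule stated |

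The abstract takes as its comparison group what the benchmark section treats as the numerator of a proportion.

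**3. How many are left out.** Using the protocol's 39%: 100% − 39% = 61% of KEYNOTE-006 responders fall outside the abstract's definition. The protocol does not break this down. Some of these patients would have left before response confirmation and could never have been Safe Stop candidates. Assume (not in the documents) that a share e of all responders left before that point. The share excluded among those who reached it is then (61 − e) / (100 − e):

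- e = 0: 61/100 = 61%
- e = 10: 51/90 = 57%
- e = 20: 41/80 = 51%
- e = 30: 31/70 = 44%

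So 61% is an upper bound. It is not a progression rate, since it also contains patients who stopped early for other reasons and may still have been responding.

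**4. Direction, outcome by outcome.**

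- Adverse events: patients whose toxicity ended treatment are removed from the comparator, so it looks safer than continued treatment is. This works against early stopping.
- Quality of life: patients who relapsed or tolerated treatment badly are removed. The direction is the same.
- Costs: every comparator patient has received 24 months of drug and infusions, so drug cost is at its maximum and the saving tends to look larger. Removing the costs of toxicity and later treatment lines pulls the other way. The net effect cannot be computed from the documents, but the drug component probably dominates.

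**The case against.** The strongest reply is that the completer wording is one sentence in an abstract. The body names KEYNOTE-006 and the registry without that restriction, not stopping early may be shorthand for the standard strategy, and a condensed article can leave control selection, index date and weighting to the full protocol. This stands in part: missing matching detail is no finding. What remains is that the article does state a comparator, the stated rule is biased if followed, and it conflicts with the body.

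Four stronger readings are tempting, and the documents do not support them.

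- *The primary result is judged against selected survivors.* It is not. The test uses a fixed 29%, set against a proportion of all responders.
- *The comparator's 24-month response rate is 100% by construction.* This holds only when time runs from treatment start, as under Primary endpoint: "rate of ongoing response according to RECIST v1.1 [34] at 24 months (from first start of treatment with PD-1 blockade". The abstract words the objective as "rate of ongoing responses at 24 months after discontinuation of PD-1 blockade". On that clock, the Discussion gives progression-free survival of 82–85% at 24 months after completion for responders. These two time origins themselves need reconciling. The selection problem persists under either, because completers have already passed two years without relapse or treatment-ending toxicity.
- *61% of the trial's counterparts are removed.* As shown, that is only an upper bound.
- *The comparator looks too good on every outcome.* For costs the bias probably runs the other way.

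It is also fair to note that fewer adverse events is not part of the abstract's hypothesis; the Discussion lists it as a potential advantage.

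**Conclusion.** The point holds for the secondary comparisons and as an inconsistency between abstract and body. Following the abstract, or a literal reading of the quality-of-life comparator, would condition the control group on events after the trial's entry point. Adverse-event and quality-of-life comparisons would then lean against early stopping, and the cost comparison would tend to overstate the saving. Up to 61% of responders are affected, on the assumption that the KEYNOTE-006 figure carries over to the group actually used; the true post-entry share is lower by an amount the documents do not reveal. The primary analysis, its 29% threshold, and the 190 and 200 patients are unaffected. This should be corrected before comparative results are produced, but it does not threaten the trial's main decision.

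**What to change.** Reconcile the abstract, Secondary endpoints and Control group on one comparator:

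- Select DMTR patients on first-line PD-1 monotherapy with confirmed complete or partial response who are still on treatment at a landmark matching the trial's stopping window, leaving out the trial's own participants.
- Follow them from that date regardless of later completion, progression or toxicity, and use the same time zero in the Safe Stop group.
- Adjust for complete versus partial response, time to response and the baseline factors that the registry holds.
- Apply this to what the protocol says the registry records: clinical outcomes and quality of life.
- Label any comparison with two-year completers as descriptive only.

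No new patients or visits are needed, and the data source is already planned. The cost is some extra analysis and fewer usable controls. The protocol does not say that the registry holds confirmation dates, productivity or informal care, so the landmark may need approximating and some outcomes may have no matched comparison. Controls who later stop early on individual grounds stay in, so the contrast is with usual continuation and not with a guaranteed two years; the report should say so.

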**Discussion:**

From a patient, healthcare, and economic perspective, shorter treatment duration is preferred and overtreatment should be prevented. If early discontinuation of first-line PD-1 blockade appears to be safe, early discontinuation of PD-1 blockade may be implemented as the standard of care in a selected group of patients.

**Trial registration:**

The Safe Stop trial has been registered in the Netherlands Trial Register (NTR), Trial NL7293 (old NTR ID: 7502), https://www.trialregister.nl/trial/7293. Date of registration September 30, 2018.

## Background

Cutaneous melanoma originates from melanocytes [1]. Although melanoma has a lower incidence than other types of skin cancer, melanoma is responsible for the majority of skin cancer-related deaths worldwide, and its incidence is increasing [2, 3]. The life expectancy of melanoma patients is mainly determined by disease stage, and patients with advanced-stage disease have a significantly worse prognosis [4]. Since the introduction of immune checkpoint inhibitors (ICIs) and targeted therapies, the prognosis of patients with advanced (i.e. irresectable stage IIIC) and metastatic (i.e. stage IV) melanoma has improved significantly [5–7]. Nowadays, first-line monotherapy with the programmed cell death protein 1 (PD-1) blockers nivolumab (Opdivo®) or pembrolizumab (Keytruda®) is administered most frequently in patients with advanced and metastatic melanoma [8–10].

In the phase III registration trials [5, 11], PD-1 blockers were usually administered for up to two years or even longer [12, 13]. Interestingly, durable tumour responses have been observed after early discontinuation (< 2 years) of PD-1 blockade [14–16], not only in patients who achieved a complete response (CR) [16] but also in patients with a partial response (PR) or stable disease (SD) [17, 18]. In patients who discontinued PD-1 blockade early because of adverse events (AEs), outcomes were not compromised and tumour responses were ongoing at > 5 years after treatment commencement [5, 19–22]. Therefore, early discontinuation of PD-1 blockade is considered feasible [23], in particular since rechallenge with PD-1 blockade induces overall response rates of up to 90% in patients with progressive disease (PD) after prior discontinuation of PD-1 blockade [24]. As pre-specified criteria for (early) discontinuation of PD-1 blockade were lacking in retrospective analyses [25, 26], it is not yet known which patients can safely discontinue PD-1 blockade at an earlier time point. Based on the median time to objective response of approximately 3 months in patients with advanced melanoma [11, 27], the preferred treatment duration of PD-1 blockade is considered to be at least 3–6 months [25].

Shorter treatment duration with PD-1 blockade would yield several major advantages since the long treatment duration of PD-1 blockade has a high impact on patients, healthcare systems, and healthcare costs [28].. First, treatment with PD-1 blockade is associated with a broad spectrum of AEs (e.g. pneumonitis, colitis, nephritis, and endocrinopathies), which can develop rapidly, severely, and can be, although rare, even fatal [29–32]. Some of these AEs can persist lifelong (e.g. hypothyroidism, type 1 diabetes). Although the incidence of these immune-related AEs is not associated with the dose of PD-1 blockade, the incidence gradually increases with treatment duration [33]. Second, PD-1 blockers are intravenously (IV) administered at the outpatient clinic regularly with intervals of 2, 3, 4, or 6 weeks, which may significantly affect patients’ health-related quality of life (HRQoL), productivity, and time of informal caregivers. Third, a treatment duration of ≥ 2 years is associated with high costs for expensive drugs, IV treatment administration, personnel, and management of treatment-related AEs.

From a patient, healthcare, and economic perspective, shorter treatment duration is obviously preferred and overtreatment should be prevented. In current clinical practice, an increasing number of physicians discontinue treatment on an individual basis in patients achieving tumour response, in case of severe toxicity, or on patients’ request [25]. However, substantial evidence about the safety of early discontinuation of PD-1 blockade is lacking. Therefore, a nationwide prospective interventional study has been initiated to generate evidence on early discontinuation of first-line PD-1 blockade in patients with advanced and metastatic melanoma. For feasible implementation in clinical practice, the study has been designed according to patients’ wishes and procedures of daily clinical practice.

## Methods

### Objectives

The primary objective is to evaluate the rate of ongoing response in patients with advanced and metastatic melanoma who early discontinue first-line monotherapy with nivolumab or pembrolizumab upon achieving CR or PR (i.e. before two years of treatment). Secondary objectives include disease outcome, AEs, and HRQoL. In addition, the impact of early PD-1 blockade discontinuation on productivity (paid and unpaid work), healthcare resources, and hours of informal care will be measured.

### Study design

#### Design

The Safe Stop trial is a nationwide, multicentre, prospective, single-arm, interventional trial in the Netherlands. According to the KEYNOTE-006 trial, the (maximum) treatment duration of PD-1 blockade has been set at two years in the Netherlands [5]. The current protocol has been developed at the 19th European Cancer Organisation - American Association for Cancer Research - European Organisation for Research and Treatment of Cancer – European Society for Medical Oncology (ECCO-AACR-EORTC-ESMO) Workshop on Methods in Clinical Cancer Research with the support of a biostatistician, melanoma surgeon, medical oncologist, and patient advocate from ESMO. As patients usually have access to long treatment duration (2 years or longer) with PD-1 blockade, randomisation to early discontinuation was considered not feasible in this setting as the sample size for a randomised non-inferiority study would have been much higher and patients may refuse the randomisation.

#### Overview of current protocol

For response evaluation after the initiation of PD-1 blockade, diagnostic computed tomography (CT) and/or magnetic resonance imaging (MRI) are required every 12 ± 1 weeks. Patients can participate after confirmed response (CR or PR) according to response evaluation criteria in solid tumours (RECIST) v1.1 [34]. When patients achieve their first CR or PR upon first-line PD-1 blockade, written patient information can be provided (see Fig. 1 for timeline and study assessments). At 6–12 (+ 1) weeks after the first documentation of CR and at 12 (±1) weeks after the first documentation of PR, tumour response needs to be confirmed according to RECIST v1.1. Patients with a confirmed response and willing to discontinue first-line PD-1 blockade are eligible for inclusion and subsequently discontinue treatment up to 6 (+ 1) weeks after first confirmation of response (CR or PR). In case patients experience PD after trial enrolment, PD-1 blockade will be restarted. Another salvage therapy is allowed at the discretion of the treating physician.

**Fig. 1 Fig1:**
[figure not shown]
Timeline & flowchart of study assessments Safe Stop trial for first two years from start of PD-1 blockade. Abbreviations: CR, complete response; CT, computed tomography; HRQoL, Health-related quality of life; PD-1 blockade, programmed cell death protein 1 blockade; PR; partial response

#### Study population

Patients are eligible for this study when the following inclusion criteria are met:
age ≥ 18 yearadvanced or metastatic cutaneous melanomacurrent monotherapy with first-line nivolumab or pembrolizumab for advanced or metastatic melanoma; previous systemic treatment, including immunotherapy, in (neo) adjuvant setting for resectable melanoma is alloweddocumented diagnostic CT or MRI at the start of PD-1 blockade with nivolumab or pembrolizumab
for patients with CR on a diagnostic CT at response evaluation, a low-dose CT (i.e. usually included for positron emission tomography [PET] using fluorine-18 fluorodeoxyglucose [^18^F-FDG]) is allowed at baselinefor patients with PR on a diagnostic CT at response evaluation, a low-dose CT (i.e. usually included for ^18^F-FDG PET) is allowed at baseline if sufficient target lesions are measurable for response evaluation according to RECIST v1.1 criteria [34]; in this specific case, the sponsor should be consulteddocumented tumour response evaluation every 12 ± 1 weeks according to RECIST v1.1 [34] using a diagnostic CT and/or MRI as per standard clinical practicehaving confirmed CR (with an interval of 6–12 [+ 1] weeks after first documentation) or an ongoing PR (with an interval of 12 [±1] weeks after first documentation) according to RECIST v1.1 [34] using a diagnostic CT and/or MRIpresence of MRI brain for the screening of brain metastases (prior to first start or discontinuation of PD-1 blockade)planned and willing to discontinue nivolumab or pembrolizumab within 6 (+ 1) weeks after first confirmation of CR or PR and within 2 years from initiation of treatmentsigned and dated informed consent form

A potential subject who meets the following criterion will be excluded from participation in this study:
concomitant systemic therapies with other anti-cancer agents, e.g. BRAF-inhibitor, anti-CTLA4 (e.g. ipilimumab), or other PD-1 blockade than nivolumab or pembrolizumab

